**Non-intervention group (Enhanced standard of care)**
After index cases have been allocated to the non-intervention group at their health facility,, a careful census of the demographic characteristics of each household member will be recorded from the index case. A single contact will be made with the non-intervention index cases at the time of randomisation. Each recruited index case allocated to the non-intervention group will be provided with a referral letter for every household member they identify, and will be requested to give the pre-printed referral letter to each person in their household. The referral letter will contain information about tuberculosis and HIV and will provide recommendation to household members, that they should be screened for TB and HIV, with details of local health facilities where screening and further care (if required) may be accessed. Additionally, the referral letter will contain guidance for health providers, including recommendations that TB screening, HIV testing and further care and prevention services (including ART and TB preventive therapy as required) should be offered as per National guidelines because the individual was exposed to a likely infectious case of TB.

After approximately a week, Study Research Assistants will make a follow up call to the index case or the caregiver of the index case to assess if the referral letters were given to household members and to confirm that any ill household members have accessed their local health facility. If they have been unable to do this, advice on locations of clinics, and other assistance will be provided telephonically. No further contact will be had with non-intervention index cases of households till the final outcome visit.

**All households: final outcome assessment visit**We will conduct an outcome household visit to all households, irrespective of their study allocation at 15 months after the recruitment of the index case and initial first visit to the household and 12 months after the second follow up visit. Although the study is unblinded, we will attempt to limit research field staff’s knowledge of initial allocation; and in training for and the conduct of the final outcome assessment we will not refer to households as intervention or non-intervention households.

Finding households of index cases can be time consuming, and ideally non-intervention households should be as similar to intervention households as possible. To try and ensure that non-intervention households are not visited by teams who have been searching for a household for longer periods than intervention households where locations are known, 2-6 months prior to the final outcome visit – if resources permit - we will send a study staff team member to locate the non-intervention houses and reintroduce the study to at least one household member. Apart from confirming the address using the what3word App, no data will be recorded.

At the final outcome visit, Research Assistants will revisit all households 1) trace all household participants, ascertain vital status and brief verbal autopsies for those who have died; 2) record episodes of TB and HIV diagnosis and when they occurred, treatment and other hospitalizations from verbal report and inspection of patient-held records; and 3) investigate participants with symptoms of TB (any of: cough, fever, weight loss, night sweats) by collecting sputum for smear microscopy, sputum culture and Xpert; and 4) encourage and offer repeat HIV testing to participants negative or not previously tested at baseline; and 5) conduct a prevalence survey for latent TB infection by testing all children under 14 years old with the tuberculin skin test, read at 48-72 hours later as described previously; 6) a livestock survey will also be done on a sub-sample of 300 households (150 households per site) assessing exposure to domestic pets and livestock and consumption of raw milk.

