## Outcomes

*Primary trial outcomes*

1. Comparison between trial groups of TB FREE SURVIVAL from two months after randomisation – to the final ascertainment visit among all household members identified at baseline – a total of 13 months. We will measure this in two ways; firstly, including TB irrespective of the diagnostic method and secondly, including only bacteriologically-confirmed cases of TB.

*Secondary trial outcomes*

1. Comparison between trial groups of the incidence of all-forms of TB over months 2-15 among household members identified at baseline
2. Comparison between trial groups of the proportion of TB cases with diagnostic delay (defined as number of days between onset of symptoms and diagnosis of anti-tuberculosis treatment) among household members identified at baseline and diagnosed with TB between baseline and month 15
3. Comparison between trial groups of the prevalence of TB infection measured by tuberculin skin test reactivity >10mm at month 15 among household children identified at baseline and aged under 14 years of age. Analysis will be done overall and stratified by age.
4. Comparison between trial groups of the prevalence (reported as a percentage of those tested) of previously undiagnosed and untreated HIV infection among household members identified at baseline and again at month 15.
5. Comparison between trial groups of the cumulative incidence of all-cause mortality among all household members identified at baseline between baseline and month 15.
6. Comparison between trial groups of the cumulative incidence of TB- and HIV-related non-traumatic mortality among all household members identified at baseline between baseline and month 15.
7. Estimation of the cost-effectiveness of the intensified housed TB and HIV case-finding and prevention activities compared to the enhanced standard of care from a societal perspective.

*Exploratory outcomes*

1. Cohort analysis of the incidence of bacteriologically-confirmed, and all-forms of tuberculosis among intervention group household members receiving and not receiving isoniazid preventive therapy stratified by HIV serostatus.
2. Cohort analysis of the proportion of household members in the intervention group with previously undiagnosed HIV infection identified at baseline who successfully initiate antiretroviral therapy by month 15.

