# Study Definitions

**Households:** Physical dwelling structures comprising of all rooms under a contiguous roofed area linked by doorways or windows through which air can pass or potentially can pass.

**Household members:** All individuals who shared household airspace for lengthy periods – either slept overnight at least once, or shared at least two meals in the same household as the index case - in the 14 days prior to the index case’s diagnosis of TB

**Incident bacteriologically-confirmed TB** will be defined by a household contact who has documented evidence of at least one of any of the following: sputum smear positive for acid-fast bacilli; or culture with growth of Mycobacterium tuberculosis confirmed on speciation; or positive Xpert MTB/Rif result; or histology or cytology suggestive of TB, regardless of whether TB treatment was initiated. We will restrict incident cases to those diagnosed on a specimen taken at least 2 months after the initial baseline household contact.

**Incident bacteriologically unconfirmed TB** will be defined by a household contact without bacteriologically-confirmed TB but who has at least one of the following: TB treatment registers, or patient held TB treatment cards indicate TB treatment was initiated; or either died or was discharged from hospital with a diagnosis of TB without laboratory confirmation.

**All forms of TB** will be defined in individuals with either bacteriologically-confirmed, or bacteriologically-unconfirmed TB.

**Prevalent *Mycobacterium tuberculosis infection*** will be defined by the presence of skin induration reaction measured to be >10mm using technique recommended by the International Union Against Tuberculosis and Lung Disease at 48-72 hours after subdermal injection of 2 TU in 0.1 ml PPD RT23/Tween 80 in children younger than 7 years of age.

**Prevalent previously undiagnosed HIV infection** will be defined by household members who, at month 15 assessment, test positive for HIV using a serial rapid diagnostic test algorithm infection, having reported never previously tested positive for HIV.

**Prevalent previously undiagnosed and untreated HIV infection** will be defined by household members who, at month 15 assessment, test positive for HIV using a serial rapid diagnostic test algorithm infection and report not currently taking antiretroviral therapy.

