Additionally, for secondary outcome 1, the analysis population will be restricted to those individuals aged less than 14 years at the time of outcome assessment at 15 months and for secondary outcome 2, the analysis population will be restricted to those individuals with a bacteriologically-confirmed TB diagnosis during the follow-up period.7. Subgroup analysis

Subgroup analysis by study site (Capricorn District and Botshabelo District) will be conducted for all outcomes, in order to assess whether the effect of the intervention differs between a high (Botshabelo) and lower (Capricorn) TB burden setting.

8. Recruitment and trial profile

A trial profile figure will be produced illustrating the following, by trial arm:

• Number of index cases screened for enrolment

• Number of index cases excluded, with reasons

• Number of index cases enrolled and randomised

• Number of household members identified at baseline

• Of those household members identified at baseline, number whose vital status can be ascertained at 15 months

• Of those household members identified at baseline, number for whom data on TB diagnosis is available at 15 months

9. Baseline characteristics and descriptive analyses

Characteristics of index cases, their households and household members identified at baseline will be tabulated and summarised by trial arm. Absolute number and proportions will be used for categorical variables, and means and standard errors, or medians and interquartile ranges will be used for continuous variables.

Characteristics to be summarised will include

Index case characteristics:

• Age

• Sex

• Source of index case

• Vital status

• Presence and duration of TB symptoms

• Treatment received

• Laboratory confirmation of TB

• Co-morbidities including HIV

• Employment status

• Income

Household characteristics:

• Number of household members

• Number of rooms, windows, external doors

• Household crowding

• Household construction materials

Household member characteristics

• Relationship with recruited index case

• Airspace sharing with recruited index case

• Presence and duration of TB symptoms

• History of previous and current HIV treatment

• History of previous and current TB treatment

• Employment status

• Income

10. Statistical analysis of outcomes

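### The month-15 untreated-HIV outcome loses members found positive at baseline in the intervention arm only; separately, the child skin-test outcome carries two age limits

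*Protocol*

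**What the plan says.** **HIV outcome.** Secondary outcome 4 in the Protocol's Outcomes section (item 3 in the Executive Summary) compares the arms on "prevalence (reported as a percentage of those tested) of previously undiagnosed and untreated HIV infection among household members identified at baseline", followed by a phrase adding month 15. Study Definitions counts a member who, at the month-15 assessment, is found to "test positive for HIV using a serial rapid diagnostic test algorithm infection and report not currently taking antiretroviral therapy". That definition does not require that the member has never tested positive before. The definition directly above it, for previously undiagnosed HIV alone, does.

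**Who is tested, and when.** Under HIV testing in Trial Procedures, all intervention household members are offered a test at baseline. For the control arm, "A single contact will be made with the non-intervention index cases at the time of randomisation"; after one telephone call at about a week there is no contact until the outcome visit. At that visit, in both arms, staff will "encourage and offer repeat HIV testing to participants negative or not previously tested at baseline". The same visit also records HIV diagnoses and treatment from verbal report and patient-held records.

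**Analysis wording.** Statistical analysis describes this outcome, in both places where it is mentioned, as undiagnosed *or* untreated HIV. The outcome lists and Study Definitions say *and*.

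**Child skin test.** Study Definitions defines prevalent infection "in children younger than 7 years of age". The Executive Summary, Objectives, the final-visit procedure and Outcomes all say under 14. Section 6, Analysis populations, states that "for secondary outcome 1, the analysis population will be restricted to those individuals aged less than 14 years at the time of outcome assessment", which is the month-15 visit. In Outcomes, however, secondary outcome 1 is "Comparison between trial groups of the incidence of all-forms of TB over months 2-15 among household members identified at baseline".

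**The concern.** The test offer at month 15 depends on the baseline result, and only one arm has baseline results. Every control member counts as not previously tested and is offered a test. Intervention members found positive at baseline are not on the list. The outcome can be met only by a positive month-15 test, so these members cannot be counted whether or not they take ART.

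For the untreated part of the outcome, being diagnosed and never treated is therefore scored like being treated. The Protocol itself regards that failure as likely: it justifies the three-month visit by earlier data in which a significant proportion of members diagnosed with TB or HIV at the baseline visit did not reach care. The outcome would hide the failure that this visit is meant to correct.

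The skin-test conflict matters because infection in children is listed as a primary objective and is part of the stated hypothesis.

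**Working it through.** The Protocol gives no prevalence, power or effect for either outcome, so there is no figure of its own to reproduce.

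**1. Inputs**
- P, HIV prevalence in household members. Not given. I assume 14.6% to 36%, the antenatal figures under Study setting, as a stand-in.
- t, the share of intervention members tested at baseline, taken as equal in positives and negatives. Not given; assumed 50% to 90%.
- a, the share of positives already on ART. It cancels from the ratio.
- Everyone offered a month-15 test accepts. Bounding case: nobody starts ART in either arm.

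**2. Outcome as written**
- Control: all are tested, so prevalence = P(1−a).
- Intervention: a fraction Pt is already known positive and leaves. Prevalence = P(1−a)(1−t)/(1−Pt).
- Ratio = (1−t)/(1−Pt).

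| P | t = 50% | t = 70% | t = 90% |
|---|---|---|---|
| 14.6% | 0.54 | 0.33 | 0.12 |
| 30.3% | 0.59 | 0.38 | 0.14 |
| 36% | 0.61 | 0.40 | 0.15 |

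For example, with P = 30.3%, t = 70% and a = 50%: control = 0.303 × 0.5 = 15.15%; intervention = 0.1515 × 0.3/(1 − 0.2121) = 5.8%. Untreated HIV is in truth the same in both arms.

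In this case the ratio is below 1 for any t above 0 and any P below 1, so the direction does not depend on the chosen values.

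**3. If members who already knew they were positive are left out of testing in both arms**
Take the share who already knew as k = 50% (assumed). Control = P(1−k)/(1−Pk); intervention = P(1−k)(1−t)/(1−Pk−P(1−k)t). The ratios run from 0.11 (P = 14.6%, t = 90%) to 0.56 (P = 36%, t = 50%). The distortion remains.

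**4. If some of those found do start ART**
Let a share s of the untreated members found at baseline start ART, with no starts elsewhere. The true ratio is 1 − ts. The written ratio stays at (1−t)/(1−Pt) for every s, so it does not respond to linkage at all. It overstates the benefit while s is below (1−P)/(1−Pt). That break-even is 0.64/0.82 = 78% at P = 36%, t = 50%, and 0.854/0.8686 = 98% at P = 14.6%, t = 90%.

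**5. Counting known positives not on ART in both arms**
Both arms give P(1−a) in the bounding case: ratio 1.00.

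**6. Skin-test population, side by side**
- Executive Summary, item 2: under 14, no age date.
- Objectives: under 14.
- Final-visit procedure: tests children under 14 at that visit.
- Outcomes, item 3: under 14, identified at baseline, no age date.
- Study Definitions: under 7.
- Analysis populations: under 14 at month 15, labelled secondary outcome 1. That number is diagnostic delay in the Executive Summary and all-forms TB incidence in Outcomes. The skin test is item 2 and item 3 respectively.

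**The case against.** **Finding undiagnosed HIV is what the intervention is for.** This stands. For previously undiagnosed HIV, members diagnosed at baseline should no longer count at month 15, and a fall is a real effect. A reader might infer that the whole HIV outcome is biased by construction; the documents do not support that. The fault is confined to the untreated component.

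**The exclusion is inferred.** This is partly right. No sentence forbids testing baseline positives; the final-visit procedure only leaves them off the offer. That this affects one arm follows from reading the baseline testing, control-arm and final-visit sections together. Diagnosis and treatment are recorded at month 15, and exploratory outcome 2 follows ART start in intervention members newly found positive. The information is therefore not lost, but the outcome definition does not use it.

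**Nobody starting ART is unrealistic.** Agreed: referral, supported access and the three-month visit are all planned. It is a bounding case, and the size rests on assumed P and t. Step 4 shows that linkage would have to be very high before the overstatement disappears.

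**The baseline comparison may be only loose wording.** This is fair. Identification at baseline is the Protocol's usual cohort label, and Study Definitions fixes the outcome at month 15 only. It is a fault only if a between-arm comparison at baseline is intended.

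**The skin-test error is clerical.** Largely so. A reader might infer that TB incidence would be restricted to children; that is unlikely, because the analysis text names the child infection outcome separately. Section 10 also cites a secondary outcome 5 on community HIV load that is in neither list, so these sections appear to follow another numbering. Nor does Outcomes say under 14 *at baseline*: it gives no age date, and that reading would admit children who turn 14 before the visit at which testing is planned.

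**Conclusion.** The concern holds for the untreated component of the month-15 HIV outcome. As written, diagnosed but untreated intervention members leave numerator and denominator, and comparable controls stay in. If nobody started ART the ratio would read 0.12 to 0.61 instead of 1.00, for assumed prevalence of 14.6% to 36% and baseline uptake of 50% to 90%. These inputs are not in the Protocol as household-member figures, so the range is illustrative. The mechanism and, in that bounding case, the direction follow from the text. The mix of *and* and *or* also leaves it open which quantity is to be estimated.

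The skin-test population is separately contradictory, under 7 against under 14, with a wrong cross-reference. Neither point touches the analysis of TB-free survival. Both should be corrected, because the Protocol itself fixes the conflicting rules.

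**What to change.** **HIV.** Replace the combined outcome by two, and reconcile *and* with *or* in the Executive Summary, Outcomes, Study Definitions and Statistical analysis:
- (a) previously undiagnosed HIV at month 15, as now defined;
- (b) untreated HIV at month 15: in both arms, every listed member known to be positive (month-15 test, study baseline test, or reported or documented earlier diagnosis) and not on ART, over all listed members with known status at month 15.

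If a between-arm comparison at baseline is intended, delete it, since controls are not tested then.

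**Skin test.** Change Study Definitions to under 14. State one age date throughout; age at the month-15 assessment, as in Analysis populations, fits the final-visit procedure. In Analysis populations, refer to the outcome by name, because no single number fits both outcome lists.

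**Cost.** Mainly wording: the final visit already records HIV diagnosis and treatment. One imbalance remains in (b): intervention members have two study-test opportunities to acquire a known status and controls have one. Add a sensitivity analysis with all listed members seen at month 15 as denominator, and report the share with known status by arm.

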**HIV testing**

All household members will be offered HIV testing after counselling, in the first instance using a serial rapid diagnostic test algorithm, the kits for which will be provided provided by the Provincial Departments of Health. Research Assistants trained and accredited in HIV testing and counselling. In line with recommendations in the World Health Organization’s HIV Testing Services Guidelines 2015, a negative A1 test result will diagnose participants as HIV-negative. Positive results to both Tests A1 and the confirmatory A2 test will diagnose participants as HIV-positive. Where results to Test A1 and A2 are discrepant, both tests will be repeated, and followed by a tie-breaker using a laboratory-based 4^th^ Generation ELISA (anticipated in <1 per 1000 participants). Couples testing will be provided if requested.

Children under 18 months of age will have a dried blood spot sample taken for HIV PCR testing as per South African National Guidelines, with testing performed at the National Institute for Communicable Diseases. Results-based post-test counselling will be offered individually in a private setting out-of-earshot and out of sight of other household members.

Participants declining HIV testing may be offered alternative laboratory-based HIV testing on either a blood specimen or an oral fluid specimen using OraQuick, OraSure Technologies –depending on their availability, with communication of results within one week, but if still reluctant to be HIV tested, will be asked to provide an anonymous oral fluid sample for HIV testing for study purposes. Those who request anonymous testing without receipt of results and those who refuse HIV testing will be encouraged to go to a HIV testing facility for testing.

All participants who test HIV positive will be referred to their nearest clinic for initiation of ART. We will draw blood specimen for CD4 count estimates -if still required by National Guidelines as these are expected to change to a test and treat approach in the near future – as soon as the participant is diagnosed with HIV. Participants who test HIV positive will receive supported access to HIV treatment, prearranged by the study at their nearest HIV care clinic.

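### Members found HIV-positive at baseline are not retested at month 15, and only the intervention arm has them, so the undiagnosed-and-untreated HIV outcome leans towards the intervention even if ART use is equal

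*Protocol*

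**What the plan says.** **Baseline, intervention arm.** Under HIV testing: "All household members will be offered HIV testing after counselling".

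**Baseline, control arm.** The enhanced standard-of-care section provides a census taken from the index case, referral letters and a call after about a week. It states "A single contact will be made with the non-intervention index cases at the time of randomisation" and, after the call, "No further contact will be had with non-intervention index cases of households till the final outcome visit". Control household members have no study HIV test before month 15.

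**Month 15, both arms.** Item 4 of the final outcome visit is to "encourage and offer repeat HIV testing to participants negative or not previously tested at baseline". Item 2 of the same list records HIV diagnoses and treatment from verbal report and patient-held records.

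**Outcome.** Secondary outcome 4 under Outcomes compares the arms on the "prevalence (reported as a percentage of those tested) of previously undiagnosed and untreated HIV infection among household members identified at baseline".

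**Case definition.** Study Definitions has two entries. *Previously undiagnosed* requires a positive month-15 test in someone who reports no earlier positive test. *Previously undiagnosed and untreated* requires that members "test positive for HIV using a serial rapid diagnostic test algorithm infection and report not currently taking antiretroviral therapy", with no condition about earlier positive tests. Both places in the statistical section that mention this outcome call it undiagnosed *or* untreated.

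**The concern.** Whether a member can be counted at month 15 depends on a baseline result that exists in one arm only. In the intervention arm, someone who tested positive at baseline and never started ART is not offered the month-15 test, so cannot meet the definition and is not among those tested. In the control arm the same person has no baseline test, is offered one at month 15, and is counted.

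The omitted group may not be small. The protocol justifies its three-month visit by saying that earlier data showed a significant proportion of members diagnosed at baseline did not reach care, though it gives no number. If treatment uptake were identical in the two arms, a planned between-arm comparison would still favour the intervention.

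**Working it through.** The protocol gives no rate, power or sample size for this outcome, so there is no stated figure to reproduce. The check asks what the outcome shows when there is no true effect on treatment.

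**Inputs**
- p, HIV prevalence among contacts: not given. Range 0.146 to 0.36, the lowest and highest antenatal figures under Study setting. Contacts include men and children, so this is only a guide.
- t, share of intervention-arm HIV-positive members found positive at the baseline study test: not given. Assumed 0.3, 0.5 and 0.7.
- u, share of HIV-positive members not on ART at month 15: set equal in both arms.

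**Formulas**
- Control: everyone is offered the test, so prevalence among those tested = p·u.
- Intervention: baseline positives are removed, so prevalence = p·u·(1-t)/(1-t·p).
- Ratio = (1-t)/(1-t·p). It does not depend on u. Equal month-15 uptake in the two arms cancels.

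**Results**

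| t | p = 0.146 | p = 0.36 |
|---|---|---|
| 0.3 | 0.70/0.956 = 0.73 | 0.70/0.892 = 0.79 (0.785) |
| 0.5 | 0.50/0.927 = 0.54 | 0.50/0.820 = 0.61 |
| 0.7 | 0.30/0.898 = 0.33 | 0.30/0.748 = 0.40 |

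**Worked case.** With p = 0.20, u = 0.30, t = 0.70: control 0.20 × 0.30 = 6.0%; intervention 0.06 × 0.30/(1 - 0.14) = 2.1%; ratio 0.35.

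**Would it reach p < 0.05?** Assume 1:1 allocation, giving 1,200 × 5.5 = 6,600 members per arm. Borrow the intracluster coefficient of 0.3 from Sample size, for a design effect of 1 + 4.5 × 0.3 = 2.35, and take month-15 test uptake of 40% to 70%. The worked case is then significant more than 99% of the time. A milder case (p = 0.146, u = 0.30, t = 0.30, plus 1% new untreated infections among the rest in both arms) gives 5.2% versus 4.1%, ratio 0.78, and is significant about 24% to 38% of the time.

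**If staff skip already-known positives in both arms.** Let d be the share of positives already known. Prevalence among those still testable is q = p(1-d)/(1-pd), and the ratio is (1-t)/(1-tq), with t now the share of undiagnosed positives found at baseline. For p = 0.146 to 0.303 and d = 0.5 or 0.7, the ratio at t = 0.5 is 0.51 to 0.55. Skipping known positives does not remove the effect.

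**Does carrying baseline positives forward cure it?** Only with full uptake. If a share v of the others accept the month-15 test, the ratio becomes (t + v(1-t))/(pt + v(1-pt)). At v = 1 it is 1.00. With p = 0.20 and t = 0.70 it is 0.91/0.742 = 1.23 at v = 0.7, and 0.82/0.484 = 1.69 at v = 0.4. The error then runs against the intervention.

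**The case against.** The strongest reply rests on the outcome's name. If it truly means undiagnosed *and* untreated, a person diagnosed at baseline is rightly not a case at month 15, and fewer such people in the tested arm is a real effect of testing. That stands for the strict reading and for the separate *previously undiagnosed* definition. It does not settle the matter. The definition that the protocol gives for the combined outcome has no never-positive condition, and the statistical section speaks of undiagnosed *or* untreated. On the strict reading the outcome says little about treatment.

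The size is also open to challenge. No document supports any value of t. Decliners may give an anonymous oral-fluid sample, which cannot mark a member as baseline-positive and so plausibly leaves that member eligible at month 15; this lowers t. At t = 0.3 the distortion is moderate.

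It is fair, too, that untreated baseline positives are not invisible. Item 2 of the outcome visit records diagnosis and treatment, and exploratory outcome 2 follows ART initiation. But the case definition does not use the item 2 data, and the exploratory outcome covers the intervention arm only, so neither corrects the comparison.

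A later analysis plan could settle the denominator. Who is offered the test, and what makes a case, are fixed in this protocol.

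**Conclusion.** The point holds for the *undiagnosed and untreated* outcome as defined. Followed as written, the plan gives an apparent benefit with no difference in ART use: a ratio of about 0.73-0.79 if 30% of intervention positives are found at baseline, 0.54-0.61 at 50% and 0.33-0.40 at 70%. The direction follows from the text. The size rests on assumed t, on antenatal prevalence standing in for contacts, and on equal month-15 uptake in the two arms.

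Four stronger inferences are not supported.
- *The spurious benefit is certain to be large.* That depends on t, which the documents do not give.
- *The trial's main conclusion is affected.* This is one secondary outcome; TB-free survival does not use it.
- *The previously undiagnosed prevalence is inflated in the intervention arm.* Its denominator does shrink, but baseline diagnosis also removes cases from the numerator. An upward net effect is not shown.
- *The testing rule reveals the arm to field staff.* The sentence beginning "Although the study is unblinded, we will attempt to limit research field staff" promises only an attempt, field teams are openly unblinded, and nothing says that staff must carry baseline results, since HIV history can be taken by report.

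**What to change.** 1. Reconcile secondary outcome 4, Study Definitions and the two statements in the statistical section on whether the outcome is undiagnosed, untreated or both.
2. For untreated HIV, apply one month-15 rule to every baseline-listed member in both arms. Ask about known HIV status and current ART, then offer a test to all who do not report a known positive result. Use as denominator all members whose status is known from that report or test.
3. Report carrying forward of baseline-positive results as a sensitivity analysis only, because such results exist in one arm.
4. Show by arm how many members were classified by report, by test, or not at all. Baseline testing makes more intervention members aware of their status, so incomplete uptake can leave a residual difference of the kind shown for carrying forward.
5. Report previously undiagnosed HIV separately, and state that baseline testing lowers it in the intervention arm by definition.

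The cost is outcome wording and a small change to the visit instructions and questionnaire. HIV diagnosis and treatment are already recorded at this visit, and members who report a known positive result need no test. It should be settled before the outcome visits, because the offer of a test cannot be changed afterwards.
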